**Table 3: Schedule of Evaluations**

| Evaluations                                              | Screening
pre-run-in
(4 weeks prior
to dosing) | Screening
run-in
(2 weeks prior
to dosing) | Day 0 (Dosing) |                   | Follow-up          |                       |                                        |
|----------------------------------------------------------|---------------------------------------------------------|-----------------------------------------------------|----------------|-------------------|--------------------|-----------------------|----------------------------------------|
|                                                          |                                                         |                                                     | Pre-dose       | Time
Post-dose | Days
1,2,3,7,14 | Months
1,2,3, etc. | EOS 1 month post iNKT
cell recovery |
| Informed Consent                                         | X                                                       |                                                     |                |                   |                    |                       |                                        |
| Medical/Surgical History abc                  | X                                                       |                                                     |                |                   |                    |                       |                                        |
| Assessment of pre-existing signs
and symptoms and AEs |                                                         | X                                                   |                | X
t = 6 hrs    | X
7,14          | X
1,2,3, etc.      | X                                      |
| Concomitant
Medications                               |                                                         | X                                                   | X              | X
t = 6 hrs    | X
7,14          | X
1,2,3, etc.      | X                                      |
| Vital Signs d                                 | X                                                       |                                                     | X              | X                 | X
7,14          | X
1,2,3, etc.      | X                                      |
| Weight                                                   |                                                         | X                                                   |                |                   |                    |                       |                                        |
| Physical Examination                                     | X                                                       |                                                     | X              |                   |                    |                       | X                                      |
| Physical Assessment                                      |                                                         |                                                     |                | X
t = 6 hrs    | X
7,14          | X
1,2,3, etc.      |                                        |
| 12-lead ECG                                              |                                                         | X                                                   |                |                   |                    |                       | X                                      |
| QuantiFERON-Gold (TB test)                               | X                                                       |                                                     |                |                   |                    |                       |                                        |
| Chest X-ray e                                 | X                                                       |                                                     |                |                   |                    |                       | X                                      |
| Hematology and Coagulation                               | X                                                       |                                                     |                | X
t= 6 hrs     | X
14            | X
1,2,3, etc.      | X                                      |
| Serum chemistry and liver function
tests f | X                                                       |                                                     |                | X
t= 6 hrs     | X
14            | X
1,2,3, etc.      | X                                      |

| Evaluations                                                                     | Screening
pre-run-in
(4 weeks prior
to dosing) | Screening
run-in
(2 weeks prior
to dosing) | Day 0 (Dosing)                 |                                                   | Follow-up             |                       |                                        |
|---------------------------------------------------------------------------------|---------------------------------------------------------|-----------------------------------------------------|--------------------------------|---------------------------------------------------|-----------------------|-----------------------|----------------------------------------|
|                                                                                 |                                                         |                                                     | Pre-dose                       | Time
Post-dose                                 | Days
1,2,3,7,14    | Months
1,2,3, etc. | EOS 1 month post iNKT
cell recovery |
| Blood for peripheral lymphocytes
by flow cytometry (FACS) assay g | X                                                       | X                                                   | X                              | X
t= 6 hr                                      | X
1,2,
7, 14    | X
1,2,3, etc.      | X                                      |
| Blood for serum and cellular
biomarkers h                         |                                                         |                                                     | X                              | X
t = 6 hrs                                    | X
7, 14            | X
1,2,3, etc.      | X                                      |
| Serum for PK i                                                       |                                                         |                                                     | X                              | X
t= 15 min,
30 min, 1
hr, 3 hr, 6
hr | X
1,2, 3,
7, 14 | X
1,2,3, etc.      | X                                      |
| Serum for ADA                                                                   |                                                         |                                                     | X                              |                                                   |                       |                       | X                                      |
| Urine (clean catch) for UA/micro
and PCR j                        |                                                         | X                                                   |                                |                                                   | X
14               |                       | X                                      |
| Pregnancy Test k                                                     | X                                                       |                                                     | X
(just prior
to dosing) |                                                   |                       |                       |                                        |
| QoL Assessments l                                                    |                                                         | X                                                   |                                |                                                   |                       | X
1,2,3, etc.      | X                                      |
| In-clinic PFTs                                                                  |                                                         | X                                                   |                                | X                                                 |                       | X
1,2,3, etc.      | X                                      |
| Daily eDiary                                                                    |                                                         | X m                                      | X n                 | X                                                 | X o        | X
1,2,3,4, etc.    | X compliance                           |

| Evaluations                  | Screening
pre-run-in
(4 weeks prior
to dosing) | Screening
run-in
(2 weeks prior
to dosing) | Day 0 (Dosing) |                   | Follow-up          |                       |                                        |
|------------------------------|---------------------------------------------------------|-----------------------------------------------------|----------------|-------------------|--------------------|-----------------------|----------------------------------------|
|                              |                                                         |                                                     | Pre-dose       | Time
Post-dose | Days
1,2,3,7,14 | Months
1,2,3, etc. | EOS 1 month post iNKT
cell recovery |
| Administration of study drug |                                                         |                                                     |                | X
t = 0        |                    |                       |                                        |

a Should ensure subject meets all inclusion criteria and no exclusion criteria

b SCD history includes frequency of vaso-occlusive crisis, history of acute chest syndrome, other known organ involvement/damage, history of transfusions, recent transfusions

c Immunization history, see Section 18.1

d Just prior to dosing, on Day 0, then every 15 minutes post dose for 1 hour or until stable, then every 30 minutes post infusion.

e PA and lateral to rule out TB or other pulmonary disease process

f Blood glucose, creatinine, uric acid, blood urea nitrogen (BUN), sodium potassium chloride, calcium, phosphorus, total protein, albumin, globulin, total bilirubin, direct bilirubin, alkaline phosphatase, lactic acid dehydrogenase (LDH), aspartate aminotransferase (AST or SGOT), alanine aminotransferase (ALT or SGPT) and CRP

g iNKT cell subsets, NK cells, total T lymphocytes, B cells, iNKT cell activation marker (CD69)

h INF $\gamma$ , F1+2, D-dimers, vWF and cytokines including INF $\gamma$

i Two aliquots for PK should be prepared (one for current analysis and one for retained). Retained samples may be used to re-test PK at end of study or for other serum test such as autoantibodies, serum cytokines or other tests required to evaluate AEs or mechanism of action of NKTT120.

j If dip is abnormal, proceed to microanalysis.

k Serum pregnancy test will be performed at screening pre-run-in and urine pregnancy test at Day 0 just prior to dosing.

l Will be administered in clinic prior to any other assessments. Instruments include PROMIS and ASCQ-Me

m Provide subject with eDiary demonstration

n Assess compliance with daily eDiary

o Restart daily eDiary on Day 2 post-dosing (assess pain, medication use, hospital/medical utilization for previous day)

## **7. SELECTION AND WITHDRAWAL OF SUBJECTS**

The inclusion and exclusion criteria will be confirmed by the Investigator or an appropriate designee of his/her study staff. Subjects enrolled into the study must meet all of the following inclusion criteria and will be excluded from participation if they meet any of the exclusion criteria. “Stable” disease is defined by exclusion criteria in Section 7.2 .

### **7.1. Subject Inclusion Criteria**

1. Adults 18-50 years of age
2. Willing and able to sign informed consent
3. Diagnosed with SCD, either HbSS or HbS/B thalassemia, based on hemoglobin analysis
4. Have measurable baseline iNKT cells determined by recognition on FACS assay of circulating peripheral blood iNKT cells measured at screening pre-run-in visit and again at the screening-run-in visit
5. Have stable SCD defined as not having experienced acute pVOC, ACS or other major or significant SCD-associated event requiring hospitalization or outpatient medical care during the month prior to enrollment.

  - History of viral infection(s) requiring ongoing treatment (e.g., HIV, HCV, HBV, HSV type 2)
  - Received any live or attenuated viral immunization within six months prior to enrollment
11. Subject is not up-to-date on CDC-recommended immunizations for adults (see 18.1) or received immunization within one month prior to enrollment
12. Major concurrent illness or medical condition that, in the opinion of the investigator, would preclude participation in a clinical study, including but not limited to:
  - Uncontrolled significant cardiovascular disease or cardiac arrhythmia or clinically relevant abnormal screening ECG
  - Serious event such as stroke, TIA, DVT or PE  $\leq 6$  months prior to enrollment
  - Significant bleeding of any cause  $\leq 6$  months prior to enrollment
  - Psychiatric, behavioral or addictive disorder that, in the opinion of the investigator, would preclude participation in a clinical study
  - Known severe pulmonary hypertension (tricuspid regurgitant jet velocity (TRV)  $\geq 3.0$  m/sec on 2-D echocardiogram or an estimated pulmonary artery systolic pressure  $\geq 40$  mmHg
  - Known severe CNS vasculopathy
  - Interstitial lung disease requiring continuous oxygen or clinically significant abnormal screening CXR or O2 saturation  $< 90\%$  on room air
13. Type 1 or type 2 diabetes

14. History of cancer
15. Known allergy or hypersensitivity to any component of NKTT120 manufacturing or formulation or has previously experienced adverse reaction to protein or biologic therapeutic or experimental agent
16. Pregnant or nursing
17. Subjects of either gender who are not using highly effective method of contraception while on study [Defined as established use of oral, injected or implanted hormonal methods of contraception or placement of an intrauterine device or intrauterine system or barrier methods of contraception such as condom or occlusive cap (diaphragm or cervical/vault caps) with spermicidal foam/gel/cream/suppository\* by subject and/or partner of subject. Also acceptable are males with appropriate post-vasectomy documentation of the absence of sperm and women who are post-menopausal or permanently sterilized (e.g., tubal occlusion, hysterectomy or bilateral salpingectomy)]  
  
\*The use of barrier contraceptives should always be supplemented with the use of a spermicide. Spermicides are not a barrier method of contraception and should not be used alone.
18. Subject has participated in a clinical trial and received an investigational product within one month, five half-lives or twice the duration of the biochemical or biological effect (whichever is longer) of the investigational product prior to the start of screening for this study
19. History of marrow or stem cell transplant

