#### **4.6.3. Potential risk specific to adults with SCD and risk mitigation**

The potential risks associated with administration of NKTT120 may be enhanced by the pathophysiology of SCD. Subjects with clinical or subclinical organ damage due to SCD may

have a worse outcome following an AE than healthy subjects without SCD. Subjects will undergo routine pre-screening for evidence of end organ damage and subjects with clinical evidence of significant end organ damage will be excluded from participation in the trial.

Patients with SCD are functionally asplenic and are at risk for infection with encapsulated bacterial organisms. Subjects with ongoing infections will be excluded from the study. All subjects must have received CDC-recommended immunizations for adults, including immunizations for streptococcus pneumonia (Pneumovax) and *N. meningitides* [Meningococcal conjugate vaccine, quadrivalent (MCV4)] unless contra-indicated (see Section 18.1). While prophylactic antibiotics are generally not used in adults with SCD, subjects currently taking prophylactic antibiotics will be allowed to participate without discontinuing prophylactic antibiotics. Subjects not currently taking prophylactic antibiotics will not be required to start prophylactic antibiotics. Subjects will be monitored throughout the study for infections.

Due to the potential risk of activation of latent TB infections, subjects will be screened for recent exposure to TB and for evidence of active or latent TB by QuantiFERON-Gold® test and chest X-ray (CXR). Subjects with a history of infection with atypical mycobacterium will be excluded from the study.

Due to the potential risk of viral infection exacerbations during the period when iNKT cells are depleted, subjects will be screened for recent exposure to childhood viral diseases, including varicella, or exposure to influenza prior to enrollment and must be current on all CDC-recommended viral immunizations for adults. The CDC recommendations for adult immunizations are provided in section 18.1. Subjects will be monitored clinically for viral infections (especially Herpesvirus family viruses) throughout the study.

Subjects with a history of cancer will be excluded from the study and subjects in the study will be clinically monitored for the emergence of cancers during follow-up, until one month after recovery of iNKT cells.

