#### **4.8. Dose Rationale**

In selecting a starting dose and planned range of doses to be studied, consideration was given to the maximum recommended safe dose (MRSD) calculated using standard approaches (FDA Guidance for Estimating the Maximum Safe Starting Dose in Initial Clinical Trials for Therapeutics in Adult Healthy Volunteers), evaluation of safety factors, and an anticipated pharmacologically active dose (PAD).

The human equivalent dose (HED) to the No Observed Adverse Effect Level (NOAEL) determined in the GLP repeat dose toxicology study in cynomolgus monkeys was 3.2 mg/kg. Using a 10-fold safety factor, the MRSD is 0.32 mg/kg. The HED of an expected PAD is 0.001 mg/kg. Therefore, the planned starting dose of 0.001 mg/kg is 1/300th of the MRSD and 1/3,000th of the NOAEL.

The highest planned study dose of 0.1 mg/kg is 1/3rd of the MRSD. Therefore, the planned dose range provides for an expected margin of safety at the lowest and highest doses. However, as described in [Sections 6.1](#) and [6.6](#) of this protocol, the planned doses may be revised based on the evolving understanding of both safety and pharmacologic activity obtained throughout the study.

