### **6.2.2. Treatment and follow-up**

Treatment consists of a single IV dose of NKTT120 administered slowly over ten (10) minutes. Each subject will be followed until one month after iNKT cells have recovered to detectable levels. Total duration of follow-up post-dosing will vary based on the dose level received. Currently it is anticipated that iNKT cells will return to detectable levels within 1 month after NKTT120 is no longer detectable in the serum; in the lower dose cohorts; at the highest dose (0.1 mg/kg) this could be  $\geq 6$  months based on preliminary PK in non-human primate).

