### **6.6. Dose Adjustment Criteria**

The lowest dose is based on the lowest dose of NKTT120 in the non-GLP cynomolgus monkey studies that resulted in 50% depletion of peripheral iNKT cells within 24 hours of dosing and their return to 80% of baseline by day four post-dosing. This dose represents the lowest pharmacologically active dose in cynomolgus monkeys. The highest proposed dose level (0.1 mg/kg,) is a dose level that might deplete iNKT cells in tissue for up to four months or longer; administering this dose to subjects would be contingent on the predicted exposure being less than that associated with the no adverse effect level (NOAEL) dose determined in the nonclinical GLP toxicology studies.

As the study progresses, the current dose escalation plan of approximately half log increment may be reduced to a slower arithmetic increment of dose escalation without increasing the number of maximum subjects if required due to information based on iNKT recovery times from the lower dose cohorts. Similarly, a dose de-escalation using 3+3 enrollment will be applied if indicated by the data and recommended by the Clinical Investigators and/or SRC.

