#### 8.2.2. Permitted Medications

All concurrent medications prescribed for SCD or other medical conditions must be at stable doses for at least three months prior to enrollment the study. The following medications are permitted but not required during the study:

- Hydroxyurea (stable dose for two months prior to dosing)
- Antibiotic prophylaxis
- Vitamin D
- Calcium supplement
- Medications for treatment of hypercholesterolemia or hypertriglyceridemia (i.e., statins)

- Pain medications including: NSAID, non-narcotic analgesics, short-acting opioids, long-acting opioids
- Anti-hypertensives: e.g., angiotensin converting enzyme inhibitors, aldosteronereceptor blockers
- Inhaled SABA
- Corticosteroid (oral or inhaled), prednisone (or prednisone equivalent), 10 mg/day.
- Therapies to treat neuropathic pain such as: antidepressants (amitriptyline and nortriptyline), anticonvulsants (gabapentin (Neurontin®) pregabalin (Lyrica®), carbamazepine, felbamate, valproic acid, clonazepam and phenytoin)
- Medications to treat study-emergent adverse events

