### **8.2.3. Prohibited Medications and Treatments**

The following medications and treatments are prohibited for the duration of the trial:

- Routinely scheduled blood transfusions as part of chronic blood transfusion therapy
- Erythropoietin
- Corticosteroids (oral, parenteral or inhaled), greater than 10 mg/day prednisone or prednisone equivalent)
- Any experimental agent or drug
- Any broadly immunosuppressive drug or biologic
- Homeopathic medications, unless approved by the investigator

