#### FOOTNOTES:

(Influenza vaccine) There are four different flu vaccines available—talk to your doctor or nurse about which flu vaccine is right for you.

(HPV vaccine for men) There are two different kinds of HPV vaccine but only one HPV vaccine (Gardasil®) can be given to men. Gay men or men who have sex with men who are 22 through 26 years old should get HPV vaccine if they haven't already started or completed the series.

(MMR vaccine) If you were born in 1957 or after, you should have already gotten MMR vaccine. Talk to your doctor or nurse about how many doses you may need.

If you are travelling outside of the United States, you may need additional vaccines. Ask your doctor or nurse which vaccines you may need.

For more information, call toll free [name] ([name]) or visit <http://www.cdc.gov/vaccines>

[figure not shown]

U.S. Department of  
Health and Human Services  
Centers for Disease  
Control and Prevention

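### Live or attenuated viral vaccines are barred for six months before enrollment, but no visible text restricts them during the iNKT-depletion period that follows dosing

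*Protocol*

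**What the plan says.** **At entry.** Section 7.2, item 10, excludes a subject who meets this sub-criterion: "Received any live or attenuated viral immunization within six months prior to enrollment". The synopsis has the same criterion. The window ends at enrollment. Item 11 of 7.2 also excludes anyone immunized in the month before enrollment or not current on CDC-recommended adult immunizations.

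**On study.** Section 8.2.3 opens with "The following medications and treatments are prohibited for the duration of the trial" and then names scheduled chronic transfusion, erythropoietin, corticosteroids above 10 mg/day prednisone equivalent, experimental agents, broadly immunosuppressive drugs or biologics, and homeopathic products not approved by the investigator. No vaccine appears. Section 8.2.2, introduced by "The following medications are permitted but not required during the study", does not mention vaccines either.

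**Where the risk is placed.** Section 4.6.3 introduces its viral screening and immunization requirements with "Due to the potential risk of viral infection exacerbations during the period when iNKT cells are depleted".

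**How long depletion may last.** On the return of detectable iNKT cells, 6.2.2 says "at the highest dose (0.1 mg/kg) this could be" 6 months or more. Section 6.6 says the same dose "might deplete iNKT cells in tissue for up to four months or longer".

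**The concern.** The restriction stops at enrollment, shortly before the period in which the protocol itself locates the viral risk. As written, a site that gave a live viral vaccine to a subject whose iNKT cells were depleted would breach no listed restriction.

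What is at stake is subject safety in a first-in-human study of functionally asplenic patients. Grade 3 or 4 infections within two weeks of dosing go to the Safety Review Committee as possible DLTs (6.6.1), and later serious infections can feed the stopping rule (6.7.1). An infection following a live vaccine would therefore add an avoidable question of attribution.

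**Working it through.** The protocol has no figure to reproduce. The check compares the sections and adds two durations.

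**1. Does any 8.2.3 entry cover a licensed live vaccine?** Transfusion, erythropoietin, corticosteroids and homeopathic products do not. The entry on experimental agents does not reach a licensed vaccine. The entry on drugs or biologics is limited to broadly immunosuppressive ones, which a vaccine is not. Result: 0 of 6 entries apply.

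**2. How are comparable entry exclusions handled?**

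| Exposure | Barred at entry (7.2) | Barred on study (8.2.3) |
|---|---|---|
| Corticosteroids above 10 mg/day | item 6 | yes |
| Chronic scheduled transfusion | item 2 | yes |
| Investigational products | item 18 | yes |
| Live or attenuated viral vaccine | item 10 | no |

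Three comparable exposures are carried from entry into the study period, and the live-vaccine bar is not. No reason is given for the difference.

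**3. Is the restriction stated elsewhere?** The other mentions of immunization are in 4.6.3 (must be current), 8.2.1 (required unless contraindicated), Table 3 footnote c and 11.1.1 (history taking), and 18.1. The visible 18.1 footnotes are general patient information. On influenza they say "talk to your doctor or nurse about which flu vaccine is right for you" and give no instruction to avoid a live product. None of these places limits vaccination after enrollment. The 18.1 chart itself is not shown.

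**4. Timing.**
- Restricted before enrollment: 6 months.
- Restricted after enrollment: 0 months.
- Time from dosing to detectable iNKT cells at 0.1 mg/kg: possibly 6 months or more (6.2.2).
- Time from recovery to EOS: 1 month (6.2.2).
- Unrestricted time from dosing to EOS at 0.1 mg/kg: 6 + 1 = 7 months or more, of which 6 or more are depletion and 1 follows recovery.
- Any interval from enrollment to dosing is added to this. Section 6.2.1 puts screening in the month before dosing, so this is at most about 1 month.

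**The case against.** The strongest reply is that the protocol never says why the entry bar exists and never describes a live-vaccine hazard under iNKT depletion. In 7.2 the bar sits under current infection, which would also fit a clean-baseline screen. The 4.6.3 sentence concerns recent exposure to natural viral disease such as varicella and influenza, not vaccine virus. The risk evidence is limited too. Section 4.6.2.2 ties viral susceptibility mainly to the herpesvirus family, often with combined NK and NKT defects. Section 4.6.2.1 reports no signs of infection in monkeys depleted for more than four months, and 4.6.2 says the risk may be low. All of this stands, and it keeps the point minor. It does not explain why an exposure thought worth a six-month bar before enrollment is left open once depletion begins.

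Partial controls also exist. An investigator may judge a vaccine contraindicated under 8.2.1. Concomitant medications are reviewed on days 7 and 14, monthly and at EOS (Table 3), and 4.6.3 calls for monitoring of viral infections throughout. Absence from the permitted list in 8.2.2 is not permission. These measures lessen the consequence, but none forbids the exposure.

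A reader might infer from 8.2.1 and the influenza footnote that the protocol steers sites toward live vaccination on study. The documents do not support that. Section 8.2.1 is a condition of participation with an exemption, and the footnote is general CDC text, not a trial instruction.

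**Conclusion.** The point holds as a gap in the conduct rules: an exposure barred for six months before enrollment is not visibly restricted afterwards, including during the depletion period that 4.6.3 identifies. It is a minor, low-frequency safety matter. How often a live vaccine would fall due on study is not stated. It is probably uncommon, because entrants must already be current and only 30 single-dose subjects are planned.

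The conclusion rests on the visible text. The 18.1 chart, the Investigator Brochure and the Pharmacy Manual could contain a restriction. The duration rests on the 6.2.2 projection for 0.1 mg/kg, which the protocol bases on preliminary non-human-primate data.

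Three stronger readings are not supported:
- **A contradiction.** No sentence permits or requires live vaccines after enrollment, so nothing conflicts with item 10.
- **A known duration for each cohort.** A reader might scale the monkey recovery times to the lower human doses, using the human equivalent dose in 4.8 ("determined in the GLP repeat dose toxicology study in cynomolgus monkeys was 3.2 mg/kg"). That conversion serves the toxicology margin. The protocol does not use it for depletion time, so no durations are claimed for the lower cohorts.
- **An effect on the design.** The 3+3 rule, Table 5 and the sample size do not depend on this point.

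**What to change.** Add one entry to 8.2.3: live or attenuated viral vaccines, from enrollment until EOS (iNKT recovery plus one month); inactivated alternatives are allowed. If the Investigator Brochure or the 18.1 chart already has such a restriction, cite it there.

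An occasional live vaccine would be deferred to EOS or replaced by an inactivated product. The bar would also run about a month past detectable recovery. That goes beyond the depletion period, but it gives a margin and uses a date that sites already track. No new visit, procedure or data item is needed.
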